## Abstract

**Background:**

Neck pain is a common musculoskeletal condition with a point prevalence of around 15 % in males and 23 % in females that often presents in physiotherapy practice.

Physical therapy and/or manipulation therapy is generally the first management option for patients with mechanical neck pain. Physical therapists treat mechanical neck pain with a number of interventions including joint mobilization and/or manipulation, therapeutic exercises or education. However, manipulation of the cervical spine carries some risks. Treating the thoracic spine for neck pain is an alternative approach. Emerging evidence suggests that it may be effective for treating neck pain without the risks associated with cervical spine manipulation. A new electromechanical device has recently been developed and tested for delivering multiple high velocity, low amplitude thrust manipulations to the spine. This device incorporates both auditory and visual systems that provide real time feedback on the applied treatment. The objective of this study is to compare the short- and long-term effects of manual versus mechanically assisted manipulations of the thoracic spine for neck pain patients.

**Methods/Design:**

A 6-month, randomized controlled trial consisting of 54 patients with acute or chronic neck pain patients will be conducted. Patients with no signs of major pathology and with little or no interference with daily activities will be recruited. Three treatment sessions with 4-day intervals will be carried out. The patients will be randomly assigned to receive either manually performed manipulations or electromechanical manipulations at the thoracic spine. The primary outcome is pain intensity as measured by the Visual Analogue Pain Rating Scale. The secondary outcome measures are neck physical disability using the Neck Disability Index, quality of life measured by the European Quality of Life 5 Dimensions 5 Levels and patients’ improvement using the Patient’s Global Impression of Change Scale.

**Discussion:**

It is expected that both interventions will improve neck pain. This would be a significant finding, as thoracic spine manipulation for neck pain does not carry the same risk of injury as cervical spine manipulation. In addition, the results may provide useful information about therapeutic options for health care providers and patients for the problem of neck pain.

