### Study aim

The aim of this study is to compare the short and long-term treatment outcomes for neck pain patients using an instrument-assisted mechanical manipulation with feedback versus manual manipulations of the thoracic spine.

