### Training program

After the first treatment session the patients will all be introduced to the home exercise program and asked to perform this program once a day for 6 weeks, while compliance with the home exercise program is assessed using a training journal:Retraining the cranio-cervical musclesTraining the holding capacity of the deep neck flexors [55]Head Lift [56]Retraining scapular muscles [55]Eye/Head coordination [55]

A detailed exercise-program may be found in Additional file 1.

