#### Secondary outcome measures

Secondary outcome measures are the NDI, EQ-5D-5 L and the PGIC.

The German version of NDI is a questionnaire to assess self-rated disability in neck pain patients. It is a short paper-pencil instrument, which is based on a similar instrument used for patients with lower back pain, the Oswestry Low Back Pain Questionnaire. It consists of ten items: for example, working and driving. Each item has a score up to 5 with a total score of 50. The lower the score the less the self-rated disability [42, 43].

The EQ-5D-5 L is a valid and reliable self-report questionnaire that measures patient’s health status for clinical and economic appraisal using a descriptive system and a VAS [44, 45]. The descriptive system assesses mobility, self-care, usual activities, pain, discomfort and anxiety/depression and patients choose the most appropriate option from ‘no problem’ to ‘extreme problem’. The digits for the five dimensions can be combined in a five-digit number, which describes the health status. The VAS is vertical and 20 cm long and the endpoint options range from ‘the best health you can imagine’ to ‘the worst health you can imagine’. The participant is asked to mark the scale with a ‘X’ and write the corresponding number in a box [57].

The PGIC is a valid outcome measure that is based on a seven-point Likert scale [58]. The purpose of the PGIC is to obtain a patient’s report of their improvement over time during treatment. The scale ranges from ‘much better’, ‘better’, ‘somewhat better’, ‘no change’, ‘somewhat worse’, ‘worse’ and ‘much worse’. ‘Much better’ is rated as 7 and ‘much worse’ as 1 on the PGIC [59]. With this scale it is possible to dichotomize the participants into 2 groups; namely those that have ‘improved’ (ratings of 6 and 7) and those that have ‘not improved’ (ratings 1 to 5).

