The results of this study may provide useful information for clinicians and patients in terms of effective therapeutic options for treating neck pain patients without the risk of cervical spine manipulation. The outcomes of the research will be published in a timely manner after the completion of this study**.**

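### Improvement in both arms is announced as a meaningful finding for thoracic manipulation, but the design supports only the manual-versus-mechanical comparison

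*Protocol article*

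**What the plan says.** The Discussion part of the abstract gives the expected result and its meaning: "It is expected that both interventions will improve neck pain. This would be a significant finding, as thoracic spine manipulation". The reason offered is a lower injury risk than with treatment of the cervical spine. The closing paragraph of the main Discussion returns to the theme in hedged form. It says that the results may inform readers about "effective therapeutic options for treating neck pain patients without the risk of cervical spine manipulation".

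The design is a comparison of two active treatments. The abstract's Methods/Design states: "The patients will be randomly assigned to receive either manually performed manipulations or electromechanical manipulations at the thoracic spine". The Study aim is to compare outcomes "using an instrument-assisted mechanical manipulation with feedback versus manual manipulations of the thoracic spine". Exercise is common to both arms. Under Training program: "After the first treatment session the patients will all be introduced to the home exercise program", to be done once a day for 6 weeks. The main Discussion explains that exercise was added because the combination is thought to give the greatest benefit.

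The primary outcome is the pain VAS, and "Secondary outcome measures are the NDI, EQ-5D-5 L and the PGIC". Under Statistical methods, the sample size is set for a 12 mm mean difference with a standard deviation of 15 mm, and VAS changes are tested by the group-by-time interaction in a repeated-measures ANOVA. Secondary outcomes are to be compared with a Wilcoxon test for matched pairs.

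**The concern.** That both arms improve is a statement about change within each arm. The aim, the sample size and the primary test are about a difference between arms. The announced interpretation therefore rests on a contrast that randomisation does not protect.

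Several things other than manipulation can lower pain in both arms at once. Patients enter through private practices with acute or chronic neck pain, so natural recovery and regression to the mean are to be expected. Everyone also exercises daily for 6 weeks, and the article itself expects exercise to add benefit. At most, the change across the first session precedes the exercises, and that change has no control either.

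A plausible outcome is that both arms fall and do not differ clearly. Read as the abstract suggests, that result would be reported as showing that thoracic manipulation works. It would be equally compatible with no effect of manipulation.

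**Working it through.** **1. The plan's own figure.** Inputs from Number of test subjects: two-sided 5% level (1.96), 80% power (0.842), standard deviation 15 mm, difference 12 mm.

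2 × (1.96 + 0.842)² × 15² / 12² = 24.535, so 25 per arm. Adding 2 per arm gives 27 per arm and 54 in total. The figure reproduces, and it is for a difference between two arms.

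**2. Which statement each part of the plan can support.**

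| Part of the article | Contrast addressed |
|---|---|
| Study aim | manual versus mechanical |
| Sample size | 12 mm between arms |
| ANOVA, group × time | manual versus mechanical |
| Wilcoxon matched pairs (secondary outcomes) | change within patients |
| Abstract, Discussion | improvement within both arms |

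The two arms contain different, unpaired patients. A matched-pairs test can therefore only compare patients with themselves over time, so it points towards the same uncontrolled contrast as the abstract.

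**3. How easily both arms improve with no effect of manipulation.** Assumptions, none of them given in the article:
- 25 analysed patients per arm and independent arms;
- a two-sided 5% paired t test in each arm;
- a shared mean fall *m* unrelated to manipulation;
- a standard deviation of change *s* of 15 or 20 mm. The article's 15 mm is described as the standard deviation of a VAS, not of change.

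The non-centrality is m / (s/√25), and the critical value on 24 degrees of freedom is 2.064. The chance that both arms are significant is the square of the power in one arm.

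| m (mm) | s (mm) | Non-centrality | One arm | Both arms |
|---|---|---|---|---|
| 8 | 15 | 2.667 | 0.725 | 0.53 |
| 10 | 15 | 3.333 | 0.892 | 0.80 |
| 12 | 15 | 4.000 | 0.970 | 0.94 |
| 8 | 20 | 2.000 | 0.484 | 0.23 |
| 10 | 20 | 2.500 | 0.670 | 0.45 |
| 12 | 20 | 3.000 | 0.821 | 0.67 |

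For a 10 mm shared fall the range is 45% to 80%. A normal approximation gives 50% to 84%.

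**4. What the trial can say.** With the planned 15 mm and 25 per arm, the 95% confidence interval for a single between-arm difference has a half-width of about 1.96 × 15 × √(2/25) = 8.3 mm. A non-significant difference would thus leave room for a sizeable one. The interval, not the absence of significance, should carry the conclusion.

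**The case against.** The strongest reply is that the sentence is an expectation in an abstract, not a decision rule. Everything that fixes the inference is between-arm, and the main Discussion opens by restating that comparison. A trial of two delivery methods needs no sham or untreated arm for its aim, and exercise common to both arms does not bias the contrast. All of this stands. The primary analysis, allocation and sample size are not at fault, and no further arm is needed.

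It is also fair that the illustration uses a within-arm t test on the VAS, which the plan does not name, and a shared fall with no source in the article. The figures show that the announced result can arise without any effect of manipulation. They do not predict this trial.

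The reply does not remove the point. The sentence is the abstract's only statement of what the expected result would mean, and the planned matched-pairs test would supply numbers for that reading.

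Two stronger readings are tempting and are not supported:
- **That the trial plans to conclude on safety.** The lower risk is given as the reason why improvement would matter, and it rests on the Background's discussion of the literature. No part of the article says that risk will be compared, and the closing sentence of the Discussion is hedged.
- **That harms go unrecorded because no harm outcome is listed.** The article condenses a fuller protocol that is not shown, and adverse-event recording may well be there.

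**Conclusion.** The concern holds as one of interpretation. Calling improvement in both arms a significant finding for thoracic manipulation goes beyond a design with two active arms, shared exercise and no untreated or sham control. With 25 per arm, a standard deviation of change of 15 to 20 mm and a 10 mm shared fall unrelated to manipulation, both arms would improve significantly in about 45% to 80% of trials. Over shared falls of 8 to 12 mm the range is 23% to 94%. These figures depend entirely on the assumed values. The logical point does not: no size of within-arm fall would identify an effect of manipulation here. The manual-versus-mechanical comparison is unaffected, and no change in sample size follows.

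**What to change.** Revise the Discussion part of the abstract and the closing paragraph of the main Discussion to say three things:

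1. Conclusions rest on the difference between manual and mechanical manipulation in VAS, and in the secondary outcomes, each with its 95% confidence interval.
2. Change within each arm is descriptive and cannot be attributed to manipulation, because exercise, natural course and regression to the mean act in both arms.
3. The lower risk relative to cervical manipulation is background from the literature and not a result of this trial.

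For the first statement to cover the secondary outcomes, a between-arm estimate should be reported for each of them, with any matched-pairs result labelled as descriptive.

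The cost is a few sentences and a more modest stated conclusion. Recruitment, data collection and sample size stay as they are.

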**Trial registration:**

Current Controlled Trials ISRCTN88585962, registered January 2013

**Electronic supplementary material:**

The online version of this article (doi:10.1186/s13063-015-0763-5) contains supplementary material, which is available to authorized users.

## Background

The burden of musculoskeletal disorders is increasing rapidly, using a high percentage of health care resources [1]. Neck pain is a musculoskeletal disorder and is a common cause for patients seeking treatment from health care providers [2]. Most people will see a medical practitioner or another health care provider at least once in their lifetime due to neck pain [1]. Alarmingly, 30 to 50 % of the general population suffer from neck pain annually, with a point prevalence of around 15 % in males and 23 % in females; and these numbers are increasing [1, 3]. Even more concerning is the fact that someone who has experienced one episode of neck pain is likely to have another episode within the next 1 to 5 years [4], and can be expected to suffer for several years, with a low chance of full resolution.

Neck pain is generally described as pain perceived in the posterior region of the cervical spine. It is distributed between the superior nuchalline down to the first thoracic spinous process and may radiate into the head, shoulders, arms and chest [5]. The Task Force on Neck Pain and its Associated Disorders proposed the following classification for neck pain patients:Grade I: no signs of major pathology and little or no interference with daily activities. This is frequently the caseGrade II: no signs of major pathology, but with an interference with daily activities. This occurs less frequentlyGrade III: neck pain with neurological signs or symptoms (radiculopathy)Grade IV: neck pain with signs of major pathology (for example, serious instability or spinal infection) [6]

Current opinion regarding the etiology and onset of neck pain and how it is best managed varies widely, and often seems to be associated with the background and beliefs of the clinician [6, 7]. Treatments that have been recommended for neck pain within physical therapy settings so far are exercise therapy, manipulation therapy and a combination of exercise and cervical spinal manipulation as well as education: they seem to have the highest level of evidence [8]. There are also other treatment options: for example, acupuncture, cognitive/behavioural therapy, and electro-physical modalities, but so far there is conflicting evidence about their benefit [8].

Although cervical spinal manipulation is still recommended for the treatment of neck pain, there is a small risk of possible serious side-effects such as cervical artery dysfunction (CAD), lesions of the brain stem, Wallenberg syndrome or ischemic stroke [9–11]. Although these presentations are rare they should be considered as part of the patient’s assessment [11]. The literature is equivocal on a link between the use of cervical spinal manipulation and serious risks [9, 10, 12–14]. Studies show no clear relationship between cervical spinal manipulation and an arterial dissection although the manipulation process is capable of triggering such an event, because cervical spinal manipulations are comparable to minor mechanical events, which might cause arterial dissection [15, 16]. Furthermore, literature suggests that the dissection of the vertebral or carotid artery may have already been in progress before the manipulation is given due to the fact that the dissection causes pain similar to mechanical neck pain and, therefore, patients visit a chiropractor or a primary care physician because of these complaints [17, 18]. However, there is still a debate in the current research whether manipulation of the cervical spine in patients with neck pain is harmless [10].

Pre-manipulative testing and screening procedures were introduced to minimize the risk of side-effects in cervical spinal manipulations [10]. Unfortunately these procedures have shown a lack of sensitivity, specificity, and feasibility [8, 10, 15, 17, 18]. To address the issues of the risk of a serious adverse event and a lack of useful testing/screening procedures, a different treatment strategy has been utilized [19]: spinal manipulation directed at the thoracic spine instead of to the cervical spine [20]. The justification for using thoracic spinal manipulations for the treatment of neck pain is based on the biomechanical link between cervical and thoracic spine [21–23]. Normal functioning of the cervical spine depends on normal biomechanics of the upper thoracic spine. If there is any functional disturbance in the upper thoracic spine, the capacity of the muscles decreases and the range of motion of the cervical spine is impaired [23].

Within the last few years several intervention studies, systematic reviews, and meta-analyses have been conducted investigating thoracic spinal manipulations [20, 24–30]. The majority of these intervention studies were focused on patients with acute or a primary complaint of neck pain and they reported short-term outcomes [20, 24, 26]. Thus far, only 1 study has investigated patients suffering from chronic neck pain over a long-term outcome of 6 months [27]. Nevertheless, the Orthopaedic Section of the American Physical Therapy Association (APTA) included the use of thoracic spinal manipulations as a possible treatment option in their guidelines for the treatment of patients with neck pain and neck-related arm pain, although this is based on weak evidence [25]. Young and colleagues (2014) state that there is a significant amount of evidence to recommend thoracic manipulation for the treatment of mechanical neck pain, especially for short-term improvement of range of motion and disability [31].

A manipulation may be delivered manually (high velocity, low amplitude) or mechanically using spring-loaded or electromechanical devices (mechanical force, manually assisted) [32–35]. Forces applied during a manual spinal manipulation may vary somewhat from manipulation to manipulation given by one practitioner as well as between practitioners [36]. Therefore, a mechanical instrument may have less force variation and, therefore, more consistency [32]. Mechanical devices may be useful in reducing the variations in the practitioner’s performance of spinal manipulation [34]. Two randomized controlled trials have been conducted so far, comparing the outcome of manual and mechanically delivered manipulations in patients with neck pain and patients with sacroiliac joint pain [34, 35]. One study used manual manipulations compared to mechanical force, using a spring-loaded device. The manipulations were applied to the cervical spine [34]. The other study also compared manual manipulation to a mechanical-force, manually-assisted instrument (Activator Adjusting Instrument) (Activator Methods International, Ltd, Phoenix, Arizona, USA). In this study the manipulations were applied to the sacroiliac joint [35]. Both studies concluded that both methods of applying manipulations are beneficial for the patient in terms of pain reduction, range of motion and disability of the treated area [34, 35]. Although there are only two studies using different body regions and mechanical and manual manipulations in comparison, both ways of applying a manipulation seem to be beneficial.

A new electromechanical device for manipulations has recently been developed, which purports to give objective feedback to the practitioner, using an audible sign (beep) (Fig. 1). The device contains a motion sensor and a microcomputer. While the thrusts are delivered, the amount of spinal motion and the frequency of motion are identified in real time. As the vertebra rebounds, data is sent to the microcomputer. Auto-Sense Technology® (Neuromechanical Innovations, Chandler, AZ, USA) consequently adapts the amount of the subsequent thrusts. If the acceleration response has been maximized, the treatment stops automatically [37]. However, the exact effect remains unclear if this electromechanical device does what it purports to do, and if it has the same effect as manually performed manipulations.

**Fig. 1 Fig1:**
[figure not shown]
Impulse IQ®. Picture of the device that was used to conduct the mechanical manipulations

Therefore, the purpose of this study is to compare the effects of manually performed manipulations and electromechanical manipulations to the thoracic spine in neck pain patients. Short- and long-term clinical outcomes, such as neck pain and function and overall improvement, will be assessed.

### Study aim

The aim of this study is to compare the short and long-term treatment outcomes for neck pain patients using an instrument-assisted mechanical manipulation with feedback versus manual manipulations of the thoracic spine.

## Methods/Design

This study is a randomized trial comparing the treatment effects of manual versus instrument- assisted mechanical manipulations of the thoracic spine for neck pain patients. The study has received ethical approval from the Ethics Commission of the Canton of Zurich (2012-0248).

### Enrollment and eligibility criteria

Participants will be recruited by registered chiropractors and physical therapists in private practices in the canton of Zurich. A test group of 54 participants will be recruited based on the following inclusion criteria: 1) presence of acute or chronic neck pain, Grade I or II [6]; 2) aged 18 or older; 3) able to speak and read German or English; 4) no previous manual therapy applied to the thoracic spine; and 5) interested in participating in the study. Potential participants will be excluded from the study if they suffer from the following conditions: 1) severe disorders of the cervical spine such as disc prolapse, spinal stenosis, postoperative conditions in neck and shoulder areas; 2) history of severe trauma; 3) spasmodic torticollis; 4) frequent migraine headaches; 5) peripheral nerve entrapment; 6) fibromyalgia; 7) shoulder diseases (causing reduced mobility of the joint: for example, fractures, adhesive capsulitis); 8) inflammatory rheumatic diseases; 9) osteoporosis; 10) cancer and 11) be currently undergoing legal procedures resulting from their neck pain.

If and when the participant qualifies based on the above criteria and has signed the informed consent form, the recruiting chiropractor or physical therapist will inform the research assistant of their suitability for the study. The research assistant will verify the inclusion and exclusion criteria and invite the participant for the baseline assessments.

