### Randomization

A clinician, who is not involved in the study, will independently conduct the randomization procedure. A block randomization (20 blocks of 4) using a computer-based randomization program will be conducted. The original randomization list will be stored in an opaque and sealed envelope not accessible to the therapist conducting the manipulations. Eighty sequentially numbered, sealed, opaque envelopes, containing the randomized group allocation will be prepared. At the time of treatment, these envelopes will be given to the therapist applying the manipulation, immediately prior to the execution of the manipulation. The patient will be unaware of the technique that will be applied, only that the technique may either be delivered manually or with an electromechanical instrument (Impulse iQ®, Neuromechanical Innovations, Chandler, AZ, USA). To minimize any possible effects of expectations of treatment, each participant will be asked prior to the first treatment about their expectations regarding new and conventional treatments.

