### Statistical methods

#### Number of test subjects

The sample size was calculated with the formula:$$ \mathrm{n} = \mathrm{f}\left(\upalpha, \upbeta /2\right)*2*{\upalpha}^2/{\mathrm{d}}^2 $$

Therefore: 2 × [(1.96 + 0.842)^2^ × 15^2^]/12^2^ = 24.53 [60]

The significance level alpha was chosen at 5 % and the power of 80 %.

From the literature, an expected standard deviation of 15 mm of a VAS can be determined [19]. For the expected mean difference the minimal clinically significant difference (12 mm) on the VAS was determined [61]. To be able to accomplish all needed participants, 2 patients per group will be added addressing possible withdrawals, missing data, and losses to follow up [62]. Therefore, a total of 54 patients will be recruited (27 per arm).

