### Statistical analyzes

Descriptive statistics will be used to illustrate the empirical data and research population. The Shapiro-Wilk test will be used to assess whether all the variables are normally distributed. If the data is normally distributed the changes of VAS will be analyzed using analysis of variance (ANOVA) (repeated measures) to explore possible significant interaction (group x time) effects (α[1]0.05). Secondary outcome variables will be compared using the Wilcoxon test for matched pairs including confidence intervals. Participants will be sub-grouped into acute and chronic to compare the outcomes. To analyze the outcome of the PGIC, patients will be split into 2 groups (dichotomized): improved (6 and 7) and not improved (1 to 5). With the help of logistic regression, the predicted probability of the outcome will be assessed using the PGIC as dependent variables (improved/not improved). Independent variables will be age, sex, expectations, manipulation and duration of complaints. Missing data will be analyzed using an intention-to-treat method. The data will be collected, stored and analyzed in the IBM-SPSS 22 (PASW, Chicago, IL, USA) statistics program.

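### Free improvement: add chronicity and its interaction with time to the primary VAS model, because the trial mixes acute and chronic neck pain

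*Protocol article*

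**What the plan says.** - **Population** (Protocol article, Enrollment and eligibility criteria): "presence of acute or chronic neck pain, Grade I or II" are recruited together.
- **Allocation** (Randomization): "A block randomization (20 blocks of 4) using a computer-based randomization program will be conducted". There is one numbered series: "Eighty sequentially numbered, sealed, opaque envelopes, containing the randomized group allocation will be prepared". No stratification factor is named.
- **Primary analysis** (Statistical analyzes): if normally distributed, the VAS changes go into "analysis of variance (ANOVA) (repeated measures) to explore possible significant interaction (group x time) effects". No chronicity term is mentioned.
- **Where chronicity is used** (same section): "Participants will be sub-grouped into acute and chronic to compare the outcomes". For the logistic model of PGIC, "Independent variables will be age, sex, expectations, manipulation and duration of complaints".
- **Sample size** (Number of test subjects): "The significance level alpha was chosen at 5 % and the power of 80" per cent. The plan states that "an expected standard deviation of 15 mm of a VAS can be determined" and targets a 12 mm difference, so one SD and one difference serve the whole mixed population.

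**The concern.** The plan regards duration of complaints as relevant enough to model a secondary outcome and to define sub-groups. It uses the factor neither in the allocation nor in the model for the primary outcome.

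If acute and chronic patients change at different rates over six months, that difference is unexplained variation in the group x time comparison. With 54 patients, the arms can also differ noticeably by chance in their share of chronic patients, and the primary model as described would not correct the estimate for it. What is at stake is the precision of the primary comparison and the readability of a small trial's estimate, not its validity.

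**Working it through.** **1. The plan's own figure.** Inputs from Number of test subjects: z values 1.96 and 0.842, SD 15 mm, difference 12 mm.

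n per arm = 2 × (1.96 + 0.842)² × 15² / 12² = 24.535, so 25. Adding 2 gives 27 per arm and 54 in total. The stated size is reproduced. Power at 25 per arm is 80.7% by the normal approximation and 79.1% by the noncentral t (noncentrality 12 / (15 × √(2/25)) = 2.83). The t-based figure is the baseline below, except where the normal approximation is named.

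**2. Assumptions, because the protocol does not give these figures.** Half the patients are chronic (p = 0.5). D is the difference between acute and chronic patients in VAS *change*, taken as 5, 10 or 15 mm. It must be a difference in change, because a constant difference in VAS level cancels from a group x time interaction.

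**3. Gain from adjustment if 15 mm is the SD of the mixed population.** The SD within type is √(15² − p(1−p)D²). Power is for 12 mm at 25 per arm.

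| D (mm) | SD within type (mm) | Power unadjusted | Power adjusted, types balanced across arms |
|---|---|---|---|
| 5 | 14.8 | 79% | 80% |
| 10 | 14.1 | 79% | 84% |
| 15 | 13.0 | 79% | 89% |

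**4. The other reading of the 15 mm.** If 15 mm is the SD within each type, the mixed SD is √(15² + p(1−p)D²) = 15.2, 15.8 or 16.8 mm. Unadjusted power is then 78%, 75% or 70%, and adjustment brings it back to about 79%.

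**5. Cost of the unstratified list by itself.** In an adjusted analysis, chance imbalance inflates the variance on average by 1 / (1 − 1/(N−1)). With N = 50 this is 49/48 = 1.021. At SD 15 mm within type, power falls from 79.1% to 78.3% (normal approximation: 80.7% to 79.9%). Applied to step 3, the adjusted powers of 80.3%, 83.6% and 89.3% become 79.4%, 82.9% and 88.6%. The loss is under 1 point throughout.

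**6. Size of the chance imbalance.** With 27 chronic patients among 54 and 27 per arm, the arms differ by 5 or more chronic patients in about 28% of allocations. The SD of the difference in chronic share is √(4 × 0.25 / 53) = 0.137. The typical (root mean square) shift in an unadjusted estimate is therefore 0.137 × D = 0.7, 1.4 or 2.1 mm.

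**7. This shift is not a second harm.** At 27 per arm and SD 15 mm within type, the standard error is 15 × √(2/27) = 4.08 mm. Adding the 1.4 mm shift for D = 10 gives √(4.08² + 1.37²) = 4.31 mm. The mixed SD of 15.8 mm gives 15.8 × √(2/27) = 4.30 mm. The chance shift and the power loss in step 4 are the same variance seen in two ways, and must not be added together.

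**The case against.** **The design is valid as it stands.** Permuted blocks of 4 are proper 1:1 randomisation, and chance imbalance is covered by the 5% significance level. This stands in full. A reader might infer that the unstratified list biases the comparison or costs material power. The documents do not support that: it costs under 1 point, and any larger loss comes from the model.

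**Covariates belong in an analysis plan.** The article condenses its methods, and covariates for the primary model are commonly left to a document not shown here. This stands against calling the term an omission or an error. It does not defeat a suggestion, because the article states the primary model and also states where duration of complaints is used.

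**The size is assumed, and the test is simplified.** The chronic share and the difference between types are not in the protocol, and a D of 15 mm exceeds the trial's own 12 mm target. The calculation is a t-test on one change, not the repeated-measures test. Many VAS readings fall around three sessions 4 days apart, when courses have little time to diverge. This stands: the figures are an illustration, and the gain may be close to nil.

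**The plan's use of the factor is thin evidence.** Age, sex and expectations sit beside duration in the PGIC model. True, and stratifying on all of them would be impractical with 54 patients. Chronicity differs in that the plan also defines sub-groups by it.

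**Conclusion.** The point holds as a free improvement, not as an error. The trial mixes acute and chronic patients and uses that distinction elsewhere in its analysis, but the primary VAS model as described does not use it.

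If 15 mm is the SD of the mixed population and half the patients are chronic, adjustment takes t-based power from 79% to about 80%, 84% or 89% for a difference in change of 5, 10 or 15 mm. Without stratification the result is up to 1 point lower. If the two types follow the same course, there is nothing to gain beyond protection against questions about imbalance.

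Two stronger readings should be resisted:

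- **That the trial is underpowered because it pools the types.** This follows only if 15 mm is a within-type SD, which the documents do not say. If it is the SD of the mixed population, the planned power stands.
- **That stratifying would rescue the acute and chronic comparisons.** Power for 12 mm in a sub-group holding half the patients is about 52% (normal approximation, 12.5 per arm). That follows from a sample size set for the pooled comparison, and stratification would barely change it.

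**What to change.** Add chronicity (acute or chronic), or duration of complaints as already used for PGIC, to the primary repeated-measures VAS model together with its interaction with time. The interaction is the part that matters: a term for level alone does not reduce the error in the group x time test. Fix one definition before the data are examined, including the cut-off if the variable is dichotomised, and use the same definition for the planned sub-groups. The article gives no cut-off.

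The cost is one between-patient factor with its time interaction, and one or very few degrees of freedom. It needs no extra patients, visits or data.

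Splitting the remaining envelopes into acute and chronic sets is optional. Recruitment is under way, the number of patients still to be randomised is not stated, and the split would change the concealment procedure and add a classification step before allocation. On average it would gain less than 1 point of power beyond the model term.
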